### Safety monitoring and adverse events

3.6

Systematic safety assessment: Participants will be monitored for gastrointestinal symptoms (e.g., abdominal pain, diarrhea) during follow-up visits at weeks 4, 8, and 12. Liver and kidney function tests will be performed at baseline and at the end of the intervention. The onset time, severity, management, and outcomes of all adverse events will be documented in detail.

Discontinuation criteria: If more than three serious adverse events related to the intervention occur, cases will be submitted to study staff for evaluation, and the trial will be terminated if deemed necessary.

## Randomization and allocation concealment

4

### Random sequence generation

4.1

A simple randomization sequence will be generated by an independent statistician using SAS 9.4. The randomization list will be sealed and retained by the statistician in a secure location.

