**Interventions**	Group1: Omega-3 PUFA-enriched eggs group Intervention: Participants will consume one omega-3 PUFA-enriched egg daily, five days per week (Tuesday through Saturday). Monday and Sunday are designated as egg-free days, during which no eggs or egg-derived products are permitted. Concurrent use of deep-sea fish oil and other omega-3 fatty acid supplements is prohibited throughout the intervention period. Group2: Regular eggs group Intervention: Participants will consume one regular egg daily, five days per week (Tuesday through Saturday). Monday and Sunday are designated as egg-free days, during which no eggs or egg-derived products are permitted. Concurrent use of deep-sea fish oil and other omega-3 fatty acid supplements is prohibited throughout the intervention period. Group3: blank control Group Intervention: Participants will maintain their habitual dietary patterns throughout the 12-week study period. Consumption of deep-sea fish oil and other omega-3 fatty acid supplements is prohibited for the duration of the trial.
**Outcomes**	Plasma concentrations of omega-3 fatty acids, lipid metabolism indicators,inflammation and oxidative stress markers; metabolomics and gut microbiome
**Collecting samples**	Blood, Urine, Fecal samples
**Recruitment state**	Not yet recruiting
**Randomization procedure**	The randomization sequence will be generated by an independent statistician ([name], Peking University School of Public Health) who is not involved in trial conduct or outcome assessment. Using simple randomization, participants will be allocated in a 1:1:1 ratio to one of three group: (i) omega-3 PUFA-enriched eggs intervention; (ii) regular eggs group; or (iii) blank control group. Randomization will be performed via the sample() function in R software (version 4.3.1). The sequential allocation list will be encrypted and stored in a secure, access-controlled repository. To ensure allocation concealment, the randomization schedule will remain inaccessible to intervention administrators, outcome assessors, and data analysts until the completion of data collection and the prespecified unblinding procedure.

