## Study process

3

This study is designed as a community-based randomized controlled trial with a 12-week intervention period. Community-dwelling adults aged ≥ 65 years will undergo metabolic syndrome screening, including physical measurements and blood tests, to identify eligible participants based on predefined inclusion and exclusion criteria. A total of 180 participants will be enrolled and randomly allocated into three groups (60 per group) using a computer-generated randomization sequence. The total study duration will be 13 weeks, comprising a one-week baseline assessment period followed by a 12-week intervention. Follow-up evaluations and biospecimen collection will be conducted at weeks 4, 8, and 12 of the intervention, with the final assessment completed at week 13.

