### Allocation concealment and implementation

4.2

The random sequence will be sealed in sequentially numbered, opaque, tamper-evident envelopes. A non-enrolling investigator will open the envelopes and assign eligible participants to groups, while enrolling investigators will remain blinded to the allocation sequence throughout the recruitment period.

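### Simple randomisation cannot be relied on to deliver the stated 60 per group, and the protocol names two different programs for generating the one allocation list

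*Protocol article*

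**What the plan says.** **Method.** Table 1 (section 2.2) states: "Using simple randomization, participants will be allocated in a 1:1:1 ratio to one of three group". Section 4.1 also names simple randomisation. No section mentions blocks, strata, minimisation or any other restriction.

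**Group sizes.** Section 3 describes participants as "randomly allocated into three groups (60 per group) using a computer-generated randomization sequence". Section 2.3 derives 44 evaluable per group, inflates this to 59 for 25% dropout, and sets a target of 60 per group and 180 in total.

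**Generator.** Table 1 states: "Randomization will be performed via the sample() function in R software (version 4.3.1)". Section 4.1 states: "A simple randomization sequence will be generated by an independent statistician using SAS 9.4".

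**Custody and concealment.** Table 1 states: "The sequential allocation list will be encrypted and stored in a secure, access-controlled repository". Section 4.1 states: "The randomization list will be sealed and retained by the statistician in a secure location". Section 4.2 adds: "The random sequence will be sealed in sequentially numbered, opaque, tamper-evident envelopes", and then: "A non-enrolling investigator will open the envelopes and assign eligible participants to groups". Section 4.3 returns to an encrypted table held by a third-party biostatistician. The Discussion (section 8) mentions opaque envelopes again.

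**The concern.** Under simple randomisation each participant's assignment is independent of all the others, so the final arm sizes are random. A protocol cannot specify that method and also promise a fixed number per arm. Either the method is misnamed or the group size is only an expectation. Section 2.3 leaves just one participant per arm between the inflated figure (59) and the target (60), so ordinary variation in arm size can use up the margin and take the primary comparison below its planned power.

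Separately, one allocation sequence cannot have been generated both by R 4.3.1 and by SAS 9.4. Anyone who later tries to reproduce or audit the list would not know which program governs. The protocol also never says how the encrypted list relates to the envelopes.

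**Working it through.** **Inputs.** From section 2.3: N = 180, 60 per group, δ = 35 mg/dL, σ = 58 mg/dL, two-sided α = 0.05, power 80%, dropout 25%. From Table 1 and section 4.1: simple randomisation, 1:1:1.

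**Step 1. The plan's own figure.** The printed formula lacks σ², but the stated 44 uses it:

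n = 2 × (58 × (1.96 + 0.84) / 35)² = 43.06, rounded up to 44.

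44 / (1 − 0.25) = 58.7, rounded up to 59, then set at 60. The sample size reproduces.

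**Step 2. Arm sizes under simple randomisation.** The sizes follow a multinomial(180; 1/3, 1/3, 1/3).

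- SD of one arm = √(180 × 1/3 × 2/3) = 6.32; central 95% range 48 to 73.
- P(60/60/60) = 180! / (60!³ × 3¹⁸⁰) = 0.0046, about 0.5%. The approximation 3√3 / (2π × 180) gives the same value.
- P(all three arms between 55 and 65) = 34%.
- For the primary pair, P(sizes differ by 10 or more) = 39%, and by 20 or more = 7.5%.
- Expected gap between the largest and smallest of the three arms: about 13.

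**Step 3. Power for the primary pair.** With a and b randomised and 75% of each evaluable:

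power = Φ( 35 / (58 × √(1/(0.75a) + 1/(0.75b))) − 1.96 )

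| Randomised (enriched / regular) | Power |
|---|---|
| 60 / 60 | 81.7% |
| 58 / 58 | 80.4% |
| 50 / 70 | 80.6% |
| 50 / 60 | 77.9% |
| 48 / 60 | 77.0% |
| 48 / 48 | 72.6% |

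Power is below 80% when the harmonic mean of the two arm sizes is below 2 × (58 × 2.8016 / 35)² / 0.75 = 43.11 / 0.75 = 57.5.

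**Step 4. Averaging over all possible splits** (exact sum over the multinomial): mean power 81.2%; P(power below 80%) = 26%.

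**Step 5. Generator and concealment, side by side.**

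| Item | Table 1 | Sections 4.1 to 4.3 |
|---|---|---|
| Program | R 4.3.1, sample() | SAS 9.4 |
| List | encrypted, in a repository | sealed and kept by the statistician (4.1); encrypted, held by a third-party biostatistician (4.3) |
| Route to the participant | not described | numbered opaque envelopes opened by a non-enrolling investigator (4.2) |

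The first row is a contradiction. The other two can be reconciled, but the text does not do it.

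**The case against.** Simple randomisation is a valid method. It is also the least predictable one, which has some value when the blank arm is open. The expected cost is about 0.4 percentage points of power. Section 2.3 calls 60 a target, and R's sample() gives exactly 60 per arm if it permutes a list holding 60 of each code, so loose terminology may be the whole explanation. The validity, the unpredictability and the small average cost all stand. The terminology argument does not remove the point: a permuted fixed list is restricted randomisation, and both places that name the method call it simple.

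Four stronger readings are tempting, and the documents do not support them.

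- **That 59 per arm is the required size.** On that threshold at least one primary arm falls short with probability 73% (1 − 0.27). But 59 is a rounded, dropout-inflated figure; 58/58 still gives 80.4% power. The 26% is the relevant figure.
- **That two lists compete and concealment is threatened.** No section describes two lists. An encrypted master list and envelopes prepared from it can coexist, and section 4 contains both. What is missing is the link between them.
- **That chance imbalance in baseline triglycerides is uncontrolled.** Section 7 adjusts the primary model for baseline clinical parameters, and section 5.3 makes the Week 0 value part of the outcome trajectory. Imbalance is not restricted by design, but it is addressed in the analysis.
- **That lack of stratification is an error.** It is a design preference. Its feasibility is also unclear, because section 5.4 has samples stored and shipped in batches for central analysis, so a study-measured baseline value may not exist at randomisation.

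**Conclusion.** The point holds in limited form. As written, the allocation method does not guarantee the stated 60 per group; an exact 60/60/60 split has a probability of about 0.5%. The consequence is a 26% chance that power for the primary comparison is below the planned 80%, with a mean loss from 81.7% to 81.2%. This is a problem of delivering the design as stated; it introduces no bias, and inference remains valid. The R versus SAS statements are a plain contradiction. The custody and envelope statements need joining up and are not shown to conflict.

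The power figures assume that exactly 180 are randomised, that exactly 25% drop out of each arm, that the section 2.3 values of σ and δ hold, and that a two-sample normal comparison applies. They do not reflect the repeated-measures model of section 7, and random variation in dropout would remain under any allocation scheme.

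**What to change.** 1. Replace simple randomisation with a restricted scheme, in one of two forms:
   - permuted blocks with concealed, randomly varying sizes. The downside is some predictability, because assignments to the open blank arm are visible; varying and concealing the block sizes limits this.
   - one random permutation of a list holding 60 of each code. This gives exactly 60/60/60 if all 180 places are used, and 81.7% power on the section 2.3 assumptions with 45 evaluable per arm.
2. If simple randomisation is kept, describe 60 per group in sections 2.3 and 3 as an expected size.
3. Name one program and version in both Table 1 and section 4.1, and align the registry entry.
4. State once that a single encrypted master list exists, who holds it, and that the envelopes in section 4.2 are prepared from it.
5. Stratification by baseline triglycerides is optional, and only if a screening value is available when the participant is randomised.

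Table 1 gives the recruitment status as not yet started. If that is still so, the cost is a regenerated list and a few edited sentences.

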### Allocation concealment and implementation

4.2

The random sequence will be sealed in sequentially numbered, opaque, tamper-evident envelopes. A non-enrolling investigator will open the envelopes and assign eligible participants to groups, while enrolling investigators will remain blinded to the allocation sequence throughout the recruitment period.

### Blinding method

4.3

An open-label control with blinded intervention arms design will be adopted in this study. Of the three randomly allocated groups, only the blank control group will be unblinded and aware of their non-intervention status. The control group and the omega-3 PUFA-enriched eggs group will be administered using a blinded protocol, where participants will be informed that they will receive egg intervention but will remain blinded to the specific type (regular fresh eggs vs. omega-3 PUFA-enriched eggs). The two egg types will be identical in appearance and distinguished only by coded labels. Blinded personnel will also include intervention administrators, outcome assessors, and data analysts. Throughout the entire trial, intervention administrators, outcome assessors, and data analysts will be informed only of the unique identification codes of the participants and will be unaware of the intervention types corresponding to each group. The random allocation table will be encrypted and stored by an independent third-party biostatistician, and centralized unblinding will be performed only after the trial has been completed and the data have been locked.

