**Follow-up preparation (Weeks 4, 8, and 12):** Consumables (urine cups, catheters, and stool specimen containers) will be distributed before follow-up visits to remind participants to fast for the next day's physical examination and to collect morning urine and stool samples. **Quality control:** Dual reminders via telephone and in person; consumable ID and distribution registration; verification of sample labels and collection times upon arrival.	**Community physicians** Remote study staff (Daily diary review and quality control)
**Follow-up assessments (Weeks 4, 8, and 12):** Questionnaire administration, physical measurements, blood and biospecimen collection; cold chain transport of samples. **Quality control:** On-site review of questionnaire completeness; defined retest thresholds for physical measurements; end-to-end traceability of samples throughout the “labeling-registration-storage-cold chain” process.	On-site study staff (Weekly distribution of eggs and collection of diaries)
**Safety monitoring:** adverse events (e.g., gastrointestinal discomfort) will be recorded and managed during follow-up visits.. **Quality control:** Severe events will be reported according to established procedures, with discontinuation/withdrawal decisions documented concurrently.	Online surveyors and community physicians
Group B: Regular eggs group	
**Dietary intervention (egg consumption):** Tuesday to Saturday: **One boiled normal fresh egg** daily; Monday and Sunday: Egg-free days; Duration: 12 weeks. **Quality control**: Identical to Group A (consistent frequency and documentation).	Participants (eggs consumption and record-keeping) On-site study staff (Distribution of eggs and diaries; compliance monitoring and review)
**Adherence management/Visit preparation/Follow-up assessments/Safety:** Procedures and quality control measures will be identical to those in Group A (daily diary review, weekly distribution, distribution of consumables and fasting reminders before follow-up at Weeks 4, 8, and 12, sample collection on follow-up days with cold chain transport).	On-site study staff (Distribution of eggs and diaries; compliance monitoring and review)
Group C: Blank control group	

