**Usual diet:** Participants will maintain their habitual dietary patterns throughout the 12-week study period. **Quality control:** Potential contamination behaviors, including self-initiated consumption of eggs or egg products will be monitored through diaries and dietary surveys. These data will be used as covariates or for sensitivity analyses.	Participants (record-keeping)
**Follow-up assessments (Weeks 4, 8, and 12):** Follow-up visits and sample collection will be conducted at the same frequency as Groups A and B, including questionnaire administration, physical measurements, and blood, urine, and stool sample collection. All samples will be transported via cold chain. **Quality control:** Quality control procedures will be identical to those in Groups A and B, including on-site questionnaire review, threshold-based review of physical measurements, and end-to-end sample traceability.	On-site study staff (Distribution of eggs and diaries; compliance monitoring and review)
**Data management (all groups):** Data recording, review, and database lock. **Quality control:** Double data entry and review; source data verification for outlier detection.	Statistician

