For bias control, randomization sequences will be generated by independent statisticians, and allocation concealment will be ensured using opaque envelopes. Group assignment will be performed by non-enrolling investigators to minimize investigator bias. Regarding blinding, this trial will adopt an “open-label control with blinded intervention arms” design. The two types of eggs (omega-3 enriched vs. regular) will be identical in appearance and differentiated only by coded labels. Although participant blinding will not be feasible in the blank control group, the limitations of blinding will manifest in the following aspects. First, the open-label status of the blank control group will make participants explicitly aware that they are receiving no intervention, potentially inducing negative expectation effects and feelings of deprivation, which may lead to deterioration in health behaviors or reporting bias in symptom assessment. Although participants in the two blinded egg groups will be unaware of the specific egg type they receive, being informed of “receiving an egg intervention” may still generate positive expectations. The gradient distribution of expectation intensity across the three groups (hypothesized as: blank control < regular eggs < omega-3 PUFA-enriched eggs) will create an imbalance in expectation effects, making it impossible to distinguish whether between-group differences originate from the intervention itself or from differential psychological expectations. Second, participants in the control groups may voluntarily modify their dietary behaviors (e.g., increasing egg consumption) to compensate for the sense of deprivation, resulting in inter-group contamination and dilution of intervention effects. Third, despite the blinding of intervention administrators, outcome assessors, and data analysts, subjective outcome measures will remain susceptible to participant expectations; while objective biochemical indicators, although relatively robust, could still be confounded by behavioral changes in the control groups. Furthermore, divergent expectation levels among the three groups may lead to heterogeneous variance in outcome variables, and the potentially higher attrition rate in the blank control group could cause non-random missing data, threatening the validity of statistical inference. These limitations will exert multidimensional impacts on internal validity. First, expectation effects cannot be excluded as a confounding factor, meaning that the observed effects of omega-3 PUFA-enriched eggs may represent a combination of true biological effects, placebo effects, and negative expectation effects from the control group, with the weighting of each component remaining indeterminate. Second, it will limit the generalizability of the results to scenarios with uniform blinding or open-label conditions. In conclusion, the open-label status of the control group will constitute a source of systematic bias. Causal language should be used cautiously when interpreting results; priority should be given to objective biochemical indicators, and sensitivity analyses alongside process evaluations will be conducted to quantify the extent of bias. Nevertheless, allocation concealment, third-party randomization, assessor blinding, and post-data-lock unblinding will also be implemented to partially attenuate these biases.

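### The personnel-blinding claim covers all three arms, but the design can mask only enriched versus regular eggs; staff who hand out eggs know who is in the blank arm

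*Protocol article*

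**What the plan says.** Section 4.3 sets out an open-label control with two blinded egg arms. On participants, it says that "only the blank control group will be unblinded and aware of their non-intervention status". On staff, it adds: "Blinded personnel will also include intervention administrators, outcome assessors, and data analysts". For the whole trial these staff "will be informed only of the unique identification codes of the participants and will be unaware of the intervention types corresponding to each group". The Blinding row of Table 1 makes the same claim.

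The masking device in Section 4.3 is the egg itself: "The two egg types will be identical in appearance and distinguished only by coded labels".

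Table 3 allocates the work. For Group A, the follow-up task at weeks 4, 8 and 12 is listed as "Questionnaire administration, physical measurements, blood and biospecimen collection; cold chain transport of samples", and the responsible role is "On-site study staff (Weekly distribution of eggs and collection of diaries". For Group C, which is given no eggs, the follow-up role reads "On-site study staff (Distribution of eggs and diaries; compliance monitoring and review".

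Section 8 discusses bias that remains "despite the blinding of intervention administrators, outcome assessors, and data analysts". It later counts assessor blinding among four measures said to reduce, in part, the bias from the open-label arm.

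**The concern.** The staff-blinding statement refers to each group, so it covers the blank arm. The only masking described works between two kinds of egg and has no counterpart for a participant who gets no egg. The claim therefore asserts a property that the procedures cannot deliver for egg versus no egg, and the staffing table does nothing to keep assessors away from that information.

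At stake is how the blank-arm comparisons are read. Section 8 uses them to describe the effect of eating eggs as such and the combined effect of the enriched egg. An assessor who knows that a participant is untreated can influence a tape measurement, a manual pressure reading or a scored interview. If the trial reports its assessors as blinded, readers will discount that possibility without grounds.

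**Working it through.** No arithmetic bears on the contradiction itself. The check sets the blinding statement beside the procedures, role by role.

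**Intervention administrators**
- Claim (Section 4.3, Table 1): they know ID codes only and not the intervention of any group.
- Procedure (Table 3): on-site staff distribute eggs weekly to Groups A and B. Compliance is the ratio of eggs eaten to eggs required, and that denominator exists only for people assigned eggs. In Group C, eating eggs on one's own initiative is tracked as contamination.
- Result: anyone doing these tasks must know who is assigned eggs and who is not. The claim fails for the blank arm however the work is shared out.

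**Outcome assessors**
- Claim: the same.
- Procedure: Table 3 uses one role label for egg distribution in Groups A and B and for follow-up assessments in Groups A, B and C. Section 3.5 has participants measured and sampled, then given the eggs of their allocation, at the week 0 visit; later visits follow the same pattern.
- Against overlap: Section 3.5 assigns anthropometry and blood pressure to trained physicians, and Section 4.4 assigns sample collection to registered nurses.
- For overlap: Section 4.4 describes the intervention staff as physicians too, and no section says that assessors and egg handlers are different people.
- Result: Table 3 contradicts the claim, and nothing elsewhere resolves it. Shared individuals are possible but not shown.

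**Which outcomes are exposed**
- Primary (Section 5.3): fasting TG, a laboratory measure.
- Key secondary (Section 5.4): lipids, inflammation and oxidative stress, all laboratory measures.
- Exploratory (Section 5.4): glucose and insulin markers, metabolomics and microbiome, all laboratory measures.
- Unranked (Table 4, Sections 5.6 to 5.11): waist, blood pressure, MoCA, questionnaires and diet recall. These depend on an observer or interviewer to varying degrees. Blood pressure does so only when read manually, since Section 5.11 also permits an automated device.

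**Which comparisons are exposed**
- Enriched versus regular (primary, Section 5.3): both arms receive coded eggs, so not by this route.
- Enriched versus blank and regular versus blank: exposed, and both exploratory under Section 5.3.

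**Upper bound on visits**
- 60 blank-arm participants (Section 2.3) × 3 follow-up visits = 180 assessments, before dropout.

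**The case against.** The strongest reply is that Table 3 names a role, not people. Its bracketed task descriptions look like copied labels, since the Group C row mentions distributing eggs to an arm that gets none. Physicians and nurses are named for measurement and sampling elsewhere. This stands. A reader might infer from Table 3 that the same individuals hand out eggs and take the measurements, so that assessors know blank-arm status at every visit. The documents do not establish that; they show only one shared role label and no stated separation.

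Second, the design is openly called open-label for the control. Section 8 admits systematic bias, asks for cautious causal language and puts objective biochemical indicators first. This stands in part. The admission concerns what blank-arm participants know. The same section takes staff blinding as given and credits it with reducing the bias, so the disclosure does not reach this point.

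Third, every ranked outcome is a laboratory measure and the primary comparison is between the two egg arms. This stands in full and sets the limit of the point.

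Fourth, separating staff cannot blind everything. Section 3.3 has interviewers ask about eggs, and Table 3 requires egg intake in the blank arm to be recorded. This also stands. Asking participants not to mention eggs would conflict with those procedures and is no remedy.

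**Conclusion.** The personnel-blinding statement is too broad. For intervention administrators it cannot be true of the blank arm. For outcome assessors it is contradicted by the role allocation in Table 3 and is not secured anywhere else. It can hold for enriched versus regular eggs, provided the coded labels work as described.

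The reach is narrow: observer-dependent, unranked measures in two exploratory comparisons, at no more than 180 blank-arm follow-up visits. The documents give no basis for a size or direction of bias on any measure. A reader might conclude that the main result, or two of the three comparisons as a whole, is compromised. That does not follow. Laboratory outcomes are not affected by this route in any comparison, and the enriched-versus-regular comparison is not affected by it on any outcome.

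This conclusion assumes that samples are assayed under code, as Section 4.3 implies, and that the role labels in Table 3 mean what they say. If assessors are in fact separate people, the assessor part reduces to an unclear table; the administrator part remains. The correction should be made, because otherwise the trial would report a safeguard it does not have.

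**What to change.** 1. In Section 4.3, Table 1 and Section 8, limit the staff-blinding claim to egg type (enriched versus regular).
2. In Section 8, list staff awareness of blank-arm status as a limitation of both blank-arm comparisons, and stop citing assessor blinding as protection for them on observer-dependent measures.
3. Amend Table 3 so that waist, blood pressure and MoCA are taken by roles already named (the physicians of Section 3.5, the nurses of Section 4.4) who do not handle that participant's eggs or diaries. Because Section 4.4 also describes intervention staff as physicians, the separation has to be stated and not left to job title.
4. Treat diet recall and egg-intake questionnaires as unblinded for the blank arm and say so.

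The cost is a less favourable blinding statement and some scheduling on visit days. The documents give no staff numbers, so whether the rota fits existing staff needs a local check. Separation lowers the risk but does not remove it, since blank-arm participants know their status and may reveal it. Table 1 lists the trial as not yet recruiting, so the wording and the rota can both be settled before the first visit.
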